# Repair versus reconstruction for proximal anterior cruciate ligament tears: a study protocol for a prospective multicenter randomized controlled trial

**DOI:** 10.1186/s12891-021-04280-y

**Published:** 2021-04-30

**Keywords:** Anterior cruciate ligament, Anterior cruciate ligament reconstruction, Anterior cruciate ligament repair, Primary repair, Proximal tear, Knee injury, Suture repair, Remnant, Ligament preservation

## Abstract

**Background:**

For active patients with a tear of the anterior cruciate ligament (ACL) who would like to return to active level of sports, the current surgical gold standard is reconstruction of the ACL. Recently, there has been renewed interest in repairing the ACL in selected patients with a proximally torn ligament. Repair of the ligament has (potential) advantages over reconstruction of the ligament such as decreased surgical morbidity, faster return of range of motion, and potentially decreased awareness of the knee. Studies comparing both treatments in a prospective randomized method are currently lacking.

**Methods:**

This study is a multicenter prospective block randomized controlled trial. A total of 74 patients with acute proximal isolated ACL tears will be assigned in a 1:1 allocation ratio to either (I) ACL repair using cortical button fixation and additional suture augmentation or (II) ACL reconstruction using an all-inside autologous hamstring graft technique. The primary objective is to assess if ACL repair is non-inferior to ACL reconstruction regarding the subjective International Knee Documentation Committee (IKDC) score at two-years postoperatively. The secondary objectives are to assess if ACL repair is non-inferior with regards to (I) other patient-reported outcomes measures (i.e. Knee Injury and Osteoarthritis Outcome Score, Lysholm score, Forgotten Joint Score, patient satisfaction and pain), (II) objective outcome measures (i.e. failure of repair or graft defined as rerupture or symptomatic instability, reoperation, contralateral injury, and stability using the objective IKDC score and Rollimeter/KT-2000), (III) return to sports assessed by Tegner activity score and the ACL-Return to Sports Index at two-year follow-up, and (IV) long-term osteoarthritis at 10-year follow-up.

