### Recent literature on ACL repair

With the recognized relevance of tear location in ACL repair and the potential advantages of this treatment, several surgeons and researchers have pursued the concept of ACL repair of proximal tears [38–47]. Most of these studies were retrospective small case series reporting good short-term outcomes with an overall reported failure rates of 6 to 9%, reoperation rates of 0 to 4% and patient-reported outcome measures (PROMs) > 85% of the maximum score [48]. Three studies have also shown that the good outcomes are maintained at mid-term follow-up [44, 45, 49]. One prospective study has compared the outcomes of repair (*n* = 20) versus reconstruction (*n* = 20) in patients with proximal tears and reported similar outcomes regarding functional outcomes, failure rates and laxity examination [46]. However, no randomized studies or studies with sufficient number of patients to assess differences between the treatments have been performed, and a recent systematic review also concluded higher-level evidence studies for ACL repair are currently lacking [48]. Recent studies have also suggested that primary repair with suture augmentation results in lower failure rates when compared to primary repair without suture augmentation [42, 48].

The current surgical gold standard of treating ACL injuries is ACL reconstruction using autograft tissue of either hamstring tendons, patellar tendon or quadriceps tendon. As for all new surgical techniques, the outcomes of arthroscopic ACL repair need to be compared to the current gold standard in order to assess whether this treatment can be used for standard patient care. Therefore, a randomized controlled trial (RCT) comparing ACL repair with ACL reconstruction is needed. The ACL study group of the Dutch Arthroscopy Association also recently declared that “*the application of ACL repair could be considered in a medial ethical committee-approved study until there is high-grade and long-term evidence regarding the efficacy of modern-day ACL repair*.”

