### Goal and hypotheses

The goal of this multicenter non-inferior prospective randomized controlled trial is therefore to compare the outcomes of arthroscopic ACL repair with suture augmentation to ACL reconstruction for patients with proximal tears in a 1:1 allocation ratio. The primary outcome is the subjective International Knee Documentation Committee (IKDC) score and the secondary outcomes are other patient-reported outcomes, objective outcomes and return to sports. It is hypothesized that patients following ACL repair with suture augmentation have non-inferior primary and secondary outcomes when compared to ACL reconstruction due to the less invasive surgery.

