### Secondary outcomes (Table 2)

The secondary outcomes of this RCT are fourfold and consist of (I) other subjective outcomes, (II) objective outcomes, (III) return to sports, and (IV) long-term osteoarthritis.

Other collected PROMs for this study are the Knee Injury and Osteoarthritis Outcome Score (KOOS) [67] (Dutch validation [68]), Lysholm score [69] (Dutch validation [70]), and Forgotten Joint Score (FJS) [28] (Dutch validation [71]). Furthermore, patient satisfaction and pain scores are collected using a numeric rating scale (range 0 – 10).

The objective outcomes consist of failure of ACL repair/graft, reoperation, contralateral injury, and laxity. Failure is defined as a (traumatic) rerupture or symptomatic instability with activities. Reoperation is defined as any new operation on the same knee for any other reason than revision (e.g., symptomatic meniscus tear, hardware irritation, infection or stiffness/arthrofibrosis). Contralateral injury was defined as a complete ACL rupture of the contralateral ACL. Stability is defined as the laxity found with physical examination using the IKDC objective score form [72], which includes the Lachman, anterior drawer and pivot shift test, and side-to-side differences is assessed using KT-2000 or Rollimeter.

Return to sports is defined as (I) returning to sports, (II) returning to the same sport, and (III) returning to the preinjury level of sport. The preinjury and postoperative Tegner activity scale are also collected, which enables comparison with other studies [73] (Dutch validation [70]). Finally, confidence of return to sports and fear of reinjury are assessed using the ACL-Return to Sports Index (ACL-RSI) score [74] (Dutch validation [75]).

Osteoarthritis will be reviewed at 10-year follow-up. Radiographs of both knees will be performed, and the operated knee will be compared to (I) the contralateral knee if no operation occurred in that knee, and (II) the ipsilateral knee radiograph preoperatively. The Kellgren-Lawrence (KL) grade will be used to assess the incidence and grades of osteoarthritis.

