### Sample size

The sample size calculation was based on the primary outcome of this study (subjective IKDC score), similar to another RCT design on this topic [65]. It has been shown that a difference of 8.8 points in the subjective IKDC score is the minimal clinically important difference (MCID) [76]. Using this non-inferiority limit of 8.8 points, and a standard deviation of 11 points [42, 65, 77] along with a two-sided alpha of 0.05, a power of 90%, and a lost-to-follow-up rate of 10%, a total of 37 patients in each group (74 patients in total) are needed to assess the primary outcome of this non-inferiority RCT. This sample size is also sufficient for the MCID of KOOS [78] and Lysholm score [79]. Given the recent studies that showed that 30-40% of the acute tears will have repairable proximal ACL tears [50, 80], we estimate that approximately 200 patients will be needed to be screened preoperatively to achieve the sample size of 74 patients [81].

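### Non-inferiority is declared for failure, reoperation and contralateral injury, but the planned tests are tests of no difference and the sample was sized for subjective IKDC alone

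*Protocol article*

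**What the plan says.** The Methods part of the abstract frames all secondary objectives as non-inferiority: "The secondary objectives are to assess if ACL repair is non-inferior with regards to" four groups of outcomes, the second of which names failure, reoperation and contralateral injury. Under Goal and hypotheses, patients after repair are expected to "have non-inferior primary and secondary outcomes when compared to ACL reconstruction due to the less invasive surgery". The section Secondary outcomes confirms what the second group holds: "The objective outcomes consist of failure of ACL repair/graft, reoperation, contralateral injury, and laxity".

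The only numerical margin is in the section Sample size: "Using this non-inferiority limit of 8.8 points", for subjective IKDC, with "a standard deviation of 11 points", two-sided alpha 0.05, 90% power and 10% loss to follow-up. This gives 37 per arm. No rate or margin for a binary outcome enters that calculation.

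The section Statistical analysis assigns nominal variables to Pearson's chi-square test, or to Fisher's exact test when a cell is below 5. All tests are two-sided at p < 0.05.

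The only event rates for modern repair of proximal tears are in the section Recent literature on ACL repair: "overall reported failure rates of 6 to 9" per cent, and reoperation of 0 to 4 per cent, both from repair series.

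**The concern.** Chi-square and Fisher tests as planned take equality as the null hypothesis. Failing to reject equality is weak evidence of anything when few events are expected. At 6-9%, 33 patients give about 2 to 3 failures per arm (33 × 0.06 = 2.0; 33 × 0.09 = 3.0). A non-inferiority objective needs the reverse arrangement: a margin, and a confidence limit that must lie inside it. The article states the objective and a test, and the test cannot answer the objective.

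The Discussion says that non-inferiority of repair may lead to a treatment algorithm in which proximal avulsion tears are repaired in the acute setting. If failure and reoperation are part of what is called non-inferior, that claim would rest on outcomes about which 74 patients say little.

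**Working it through.** **Inputs.** From Sample size: margin 8.8, SD 11, two-sided alpha 0.05 (one-sided 0.025 for non-inferiority), power 90%, loss 10%. From Recent literature on ACL repair: failure 6-9% and reoperation up to 4% after repair. Assumed, because the article gives no figure: the same true rates after reconstruction, and margins of 5, 10, 15 and 20 percentage points.

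**1. The plan's own figure.** n per arm = 2 × (1.960 + 1.282)² × 11² / 8.8² = 32.8, so 33 evaluable. 33 / 0.90 = 36.7, so 37 randomized per arm and 74 in total. The stated size reproduces exactly for IKDC.

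**2. Precision for failure at 33 evaluable per arm.** SE = √(2p(1−p)/33); half-width = 1.96 × SE.
- p = 6%: SE = 0.0585, half-width 11.5 points.
- p = 9%: SE = 0.0705, half-width 13.8 points.

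**3. Power to show non-inferiority on failure.** Power = Φ(margin/SE − 1.96), with equal true rates.

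| Assumed margin (points) | Power at 6% | Power at 9% | n per arm for 90% power (6% / 9%) |
|---|---|---|---|
| 5 | 13% | 11% | 475 / 689 |
| 10 | 40% | 29% | 119 / 173 |
| 15 | 73% | 57% | 53 / 77 |
| 20 | 93% | 81% | 30 / 44 |

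For example, at 9% with a 10-point margin: 0.10/0.0705 − 1.96 = −0.54, and Φ(−0.54) = 0.29.

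**4. Reoperation at 4%.** Half-width 9.5 points; power 54% for a 10-point margin and 87% for a 15-point margin. The article gives no rate for contralateral injury, so nothing is calculated for it.

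**5. What the planned test would detect.** Exact enumeration of the two-sided Fisher test at 0.05, 33 per arm:
- 7% v 14%: power 5.7%, so a true doubling is missed in about 94% of trials.
- 7% v 21%: power 23.9%, so a tripling is missed in about 76%.
- With all 37 per arm evaluable: 7.4% and 29.4%.

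Applying the article's switching rule (chi-square without continuity correction when no cell is below 5, otherwise Fisher) leaves the 33-per-arm figures at 5.7% and 24.0%.

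**6. Two observed results.** Failures of 2/33 v 8/33 give Fisher p = 0.08, not significant with four times as many failures. Failures of 2/33 v 6/33 give a Newcombe 95% interval for the difference from −4 to +29 points.

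The normal approximation in steps 2 to 4 is rough at 2 to 3 expected events per arm. Steps 5 and 6 do not depend on it, apart from the uncorrected chi-square in the switching-rule check.

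**The case against.** The strongest reply is that this is a condensed article and the analysis plan is not shown. Secondary margins and a confidence-limit rule may be in that plan, so their absence here is no fault in itself. That stands. It does not remove the point, which rests on what the article does state: a non-inferiority objective, tests of no difference, and a size set on IKDC. An analysis plan could add margins but not patients.

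Second, whether the sample suffices depends on a margin that the reviewer supplies, and no document promises 90% power for secondary outcomes. This also stands. A 20-point margin would have 93% power for failure at 6%, and a 15-point margin 87% for reoperation at 4%. The shortfall is therefore shown for failure at margins of 5 to 10 points and, less severely, at 15. It is not shown for every secondary outcome.

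Third, stating margins with a confidence-limit rule is as valid a remedy as dropping the claim. Agreed; the fix allows either.

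Several stronger readings are tempting but unsupported:
- A reader might infer that the authors will take p > 0.05 as proof of non-inferior safety. The article sets no such rule; it leaves the possibility open.
- A reader might infer that the trial can never exclude an excess of failures below about 20 points. That confuses the margin needed for 90% power (19 to 23 points) with what an interval can exclude: 2/33 v 2/33 gives a Newcombe upper limit of 14.2 points.
- A reader might link failure to the historical abandonment of open repair. The Historical overview speaks of disappointing mid-term results and more reliable outcomes with reconstruction, and does not name failure.
- A reader might fault the remark "This sample size is also sufficient for the MCID of KOOS [78] and Lysholm score [79"]. It gives no values and cannot be checked, but the documents do not show that it is wrong.

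**Conclusion.** The point holds for the binary secondary outcomes. Non-inferiority is both objective and hypothesis for failure, reoperation and contralateral injury, while the stated tests address equality and the sample was fixed on another outcome. For failure, 33 evaluable patients per arm give an expected interval of about ±11.5 to ±13.8 points, wider than the failure rate itself. Power is 29-40% for a 10-point margin, and the planned test has roughly a 6% chance of flagging a doubling from 7% to 14%. These figures assume equal true rates of 6-9% for the interval and the margin calculation, and an evaluable sample after the planned 10% loss. The rates come from repair series, and the rate after reconstruction is assumed. For contralateral injury the mismatch between objective and test holds, but no size can be put on it. The primary IKDC sample-size figure is unaffected.

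**What to change.** In the abstract objectives and in Goal and hypotheses, limit the non-inferiority claim to subjective IKDC and to any secondary outcome that is given a prespecified margin and a confidence-limit rule. In the Statistical analysis section, say that failure, reoperation and contralateral injury will be reported as differences between arms with 95% confidence intervals, with no non-inferiority claim and no conclusion drawn from p > 0.05. Add one sentence: at failure rates of 6-9% in both arms, the expected half-width of the interval is roughly 11 to 14 percentage points, so smaller excesses cannot be ruled out reliably.

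No patients, visits or procedures are added. The cost is a less ambitious stated objective.

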**Discussion:**

Over the last decade there has been a resurgence of interest in repair of proximally torn ACLs. Several cohort studies have shown encouraging short-term and mid-term results using these techniques, but prospective randomized studies are lacking. Therefore, this randomized controlled trial has been designed to assess whether ACL repair is at least equivalent to the current gold standard of ACL reconstruction in both subjective and objective outcome scores.

**Trial registration:**

Registered at Netherlands Trial Register (NL9072) on 25th of November 2020.

## Background

### Historical overview of ACL repair

The first documented surgical treatment of an anterior cruciate ligament (ACL) injury consisted of open repair in 1895 when Mayo Robson repaired a proximally avulsed ACL and posterior cruciate ligament back to the femur in a 41-year old male with good outcomes at six-year follow-up [1]. In the twentieth century, Ivar Palmar [2, 3] and Don O’Donoghue [4, 5] reported on open primary repair as a treatment of ACL injuries, and in the early 1970s open primary repair became a popular treatment for ACL injuries [6–9].

Feagin and Curl were the first to present the outcomes of open repair in 1972 and noted good outcomes at short-term follow-up [8]. A few years later in 1976, however, they noted a deterioration of outcomes at mid-term follow-up in their cohort [10]. Similarly, several other surgeons and researchers noted good short-term [11–16] but disappointing mid-term outcomes [17–21]. With these disappointing results and the promising outcomes of ACL reconstruction, several (randomized) prospective studies were started in the 1980s comparing open ACL repair with open ACL reconstruction [19, 22–24]. These prospective studies noted more reliable outcomes with ACL reconstruction when compared to ACL repair, which ultimately led to an abandonment of open ACL repair and to the current gold standard of ACL reconstruction for all patients [9].

In 1991, Sherman et al. were the first analyzing the disappointing mid-term outcomes of open ACL repair by performing an extensive subgroup analysis [21]. The authors found that a trend towards better outcomes in patients with proximal avulsion type tears and good tissue quality when compared to patients with midsubstance tears and/or tears with poor tissue quality. Unfortunately, the inclusion of the aforementioned prospective trials was already completed before the study by Sherman et al. was published, and thus the prospective trials contained all tear types including patients that might not have been ideal candidates for ACL repair (i.e., those with midsubstance tears or tears with poor tissue quality).

When critically reviewing the historical literature, and bearing in mind these findings by Sherman et al., it can be noted that the results of open repair of proximal ACL tears were indeed better. A recent systematic review of all historical studies on open repair noted that outcomes of open repair of proximal ACL tears showed 83 to 90% clinical stability, 80% return to sports, 79% good to excellent Lysholm score and 86% satisfaction in 539 patients in 11 studies [25]. These findings indicate that ACL repair may have been prematurely abandoned for all tear types and perhaps may be a good treatment option for patients with proximal tears. Furthermore, outcomes of ACL repair can be expected to improve when benefiting from modern development, such as arthroscopy (instead of open repair) and modern rehabilitation (instead of casting and immobilization).

### Rationale for ACL repair

The rationale behind better outcomes of ACL repair of proximal tears compared to midsubstance tears is that better vascularity is present at the proximal end of the ligament [26] and, as a result, proximal tears have healing potential for reattachment that is similar to medial collateral ligament (MCL) tears [27]. The reason for the continued pursuit of repair as a treatment of ACL injuries can also be explained by the potential advantages of repair over reconstruction. With ACL repair, the native tissue can be preserved along with proprioception which may provide patients with a more normal feeling of the knee compared to ACL reconstruction [28, 29]. Also, ACL repair is a less invasive surgery when compared to ACL reconstruction as no (or only small) tunnels need to be drilled and no graft tissues need to be harvested, leading to lower surgical morbidity [30–33], faster return of range of motion and fewer complications [34]. Furthermore, in case of failure of both treatments, revision surgery following primary repair is expected to be similar to primary reconstruction (no or only small tunnels have been drilled or grafts harvested), whereas revision of reconstruction surgery can be complicated by tunnel malpositioning or widening and pre-existing hardware and is associated with inferior outcomes compared to primary ACL reconstruction [35–37].

### Recent literature on ACL repair

With the recognized relevance of tear location in ACL repair and the potential advantages of this treatment, several surgeons and researchers have pursued the concept of ACL repair of proximal tears [38–47]. Most of these studies were retrospective small case series reporting good short-term outcomes with an overall reported failure rates of 6 to 9%, reoperation rates of 0 to 4% and patient-reported outcome measures (PROMs) > 85% of the maximum score [48]. Three studies have also shown that the good outcomes are maintained at mid-term follow-up [44, 45, 49]. One prospective study has compared the outcomes of repair (*n* = 20) versus reconstruction (*n* = 20) in patients with proximal tears and reported similar outcomes regarding functional outcomes, failure rates and laxity examination [46]. However, no randomized studies or studies with sufficient number of patients to assess differences between the treatments have been performed, and a recent systematic review also concluded higher-level evidence studies for ACL repair are currently lacking [48]. Recent studies have also suggested that primary repair with suture augmentation results in lower failure rates when compared to primary repair without suture augmentation [42, 48].

The current surgical gold standard of treating ACL injuries is ACL reconstruction using autograft tissue of either hamstring tendons, patellar tendon or quadriceps tendon. As for all new surgical techniques, the outcomes of arthroscopic ACL repair need to be compared to the current gold standard in order to assess whether this treatment can be used for standard patient care. Therefore, a randomized controlled trial (RCT) comparing ACL repair with ACL reconstruction is needed. The ACL study group of the Dutch Arthroscopy Association also recently declared that “*the application of ACL repair could be considered in a medial ethical committee-approved study until there is high-grade and long-term evidence regarding the efficacy of modern-day ACL repair*.”

### Goal and hypotheses

The goal of this multicenter non-inferior prospective randomized controlled trial is therefore to compare the outcomes of arthroscopic ACL repair with suture augmentation to ACL reconstruction for patients with proximal tears in a 1:1 allocation ratio. The primary outcome is the subjective International Knee Documentation Committee (IKDC) score and the secondary outcomes are other patient-reported outcomes, objective outcomes and return to sports. It is hypothesized that patients following ACL repair with suture augmentation have non-inferior primary and secondary outcomes when compared to ACL reconstruction due to the less invasive surgery.

